## Abstract

**Background:**

Nonarteritic anterior ischemic optic neuropathy (NAAION) is a major cause of blindness in individuals over 50 years of age, with no available effective treatment. The oral dual endothelin receptor antagonist, bosentan, increases retinal optic nerve head blood flow in healthy humans and glaucoma patients. The objective of this trial is to assess the efficacy of bosentan administered at the acute stage in improving outcomes in NAAION patients.

**Methods:**

ENDOTHELION (ENDOTHELin antagonist receptor in Ischemic Optic Neuropathy) is a phase III, interventional, prospective, multicentre, placebo-controlled randomised double-blind clinical trial. The primary outcome is change in the visual field mean deviation (MD) at 3 months (Humphrey 30-2 SITA standard programme). Secondary outcomes include MD and visual acuity changes up to 24 months, changes in peripapillary retinal nerve fibre and macular ganglion cell layer thickness in the affected eye, as measured by optical coherence tomography, rate of NAAION bilateralisation at 2 years, and quality-of-life. Patients over 50 years of age presenting with typical NAAION of recent onset (less than 21 days) are randomly assigned to either 125 mg oral bosentan or placebo, twice a day, during 8 weeks. Besides visits during the treatment phase, patients attend follow-up visits at 2, 3, 6, 12 and 24 months. The inclusion of patients began in August 2015 at five French University hospital ophthalmology departments and two specialised ophthalmology centres. It is planned to include 86 patients in this trial. To date we have included 72 patients and 49 have completed the full follow-up process.

**Discussion:**

An endothelin receptor antagonist is a potential approach to improving the anatomical and functional prognosis of patients with NAAION. This multicentre double-blind randomised controlled trial is an opportunity to assess (1) the effect of bosentan on the structure and function of the optic nerve in NAAION, at 3 months, (2) the effect of bosentan on the bilateralisation rate at 24 months and (3) the tolerance profile of bosentan in this population.

**Trial registration:**

ClinicalTrials.gov NCT02377271. Registered on March 3, 2015.

## Administrative information

Note: the numbers in curly brackets in this protocol refer to SPIRIT checklist item numbers. The order of the items has been modified to group similar items (see https://trialsjournal.biomedcentral.com/submission-guidelines/preparing-your-manuscript#preparing+main+manuscript+text.

## Introduction

### Background and rationale {6a}

Nonarteritic anterior ischaemic optic neuropathy (NAAION) is the most frequent acute optic neuropathy after 50 years of age, with a general annual incidence worldwide of 10 per 100,000 individuals, and estimated at 6000 cases/year in France [1]. The pathophysiology of the disease is not well understood, being probably related to acute hypoperfusion in the short posterior ciliary arteries resulting in damage to the papillary microcirculation. This condition has been associated with various predisposing systemic factors [2] such as obstructive sleep apnoea syndrome (OSAS) in 75–80% cases [3–6], hypertension in 38–60% [7–10], diabetes in 12–23% [7, 8], dyslipidemia in 36–48% [10, 11] and anatomic ocular factors (small papillary excavation [12–15]).

The prognosis of NAAION is most often unfavourable, due to the irreversible loss of central visual acuity and visual field (VF). While some studies have reported slight spontaneous improvement (22%) [16], others reported no improvement or the deterioration of visual acuity (VA) or the VF [9, 17]. In eyes initially presenting minimum to slight VF defects, worsening was observed at 3 months after the first visit in 26% of cases and at 2 years in 27% of cases [16].

It is crucial to develop new therapeutic strategies for the acute stage of the disease so as to reduce optic nerve damage. Although corticosteroids and levodopa have been tried, these treatments have not been fully validated [18–23]. Other therapeutic strategies have been proposed, but their efficacy has not been demonstrated. These include posterior vitrectomy in patients with a small optic nerve head (ONH) and partial posterior detachment of the vitreous [24], radial neurotomy [25], intravitreal injection of triamcinolone [26, 27], electrical transcorneal stimulation [28], instillation of brimonidine [29] and LDL apheresis [30]. No validated treatment currently exists for this ischaemic optic neuropathy. Table 1 summarises the main recent studies on NAAION treatments.

**Table 1 Tab1:** Summary of studies on the treatment of NAAION (2008–2020)

Author (year)	Grade of evidence	Number of patients	Type of study	Treatment window (range)	Treatment (dose)	Outcome	Confounding factors considered
Guerriero (2009) [30]	III	20 treated 10 untreated	Case–control	N/A	LDL apheresis	Short-term improvement (in the 3 months after onset of the disease) in the MD (−11.08 ± 6.51 vs −16.53 ± 10.03, *P* = 0.03; −17 ± 5.24 vs −14.14 ± 9.42), but no benefit at 6 months	N/A
Modarres (2011) [31]	IV	31	Case series	(Range 3–22 days)	Intravitreal erythropoietin (2000 units)	VA improved in 27 eyes (87%), 20 eyes (64.5%) showed ≥3 lines of visual improvement at 3 months (*P* < 0.001)	N/A
Rebolleda (2013) [23]	III	10 treated 27 untreated	Case–control	2 weeks	Oral prednisolone (80 mg daily, tapering dose)	No significant difference between the median change in VA (in the treated group median change in LogMAR VA between the initial and 6-month visit was −0.032 (±0.21) [−0.3; 0.04]), in MD (in treated group median change in MD was −0.56 dB (±5.03) [−3.6; 0.7] ), in PSD (in treated group median change in PSD was −0.02 (±1.9) [−1.6; 0.6]) and average loss in RNFL (in the treated group median change in average RNFLT was 150.5 (±64.9) [119.8; 212.7])	Hypertension, diabetes mellitus, hypercholesterolaemia, aspirin use
Saatci (2013) [32]	III	17 total (16 patients)	Retrospective	(2–15 days)	Intravitreal ranibizumab (0.5 mg)	VA improvement in 14/17 (BCVA 1.45 ± 0.88 vs 0.77 ± 0.70 LogMar at 1st year), disc swelling improvement in 17 (RNFL was 210 ± 38 microns vs 57 ± 18 microns at 1st year)	N/A
Radoi (2014) [33]	III	21 treated 15 untreated	Retrospective	1 month	Intravitreal triamcinolone (4 mg)	At 6 months, higher proportion of patients with improved VA of more than 1 line (> 5 letters) in the injected group [15 patients (71%)] vs the untreated group [2 patients (13%)] (*P* = 0.0009). Mean variation of VA letters at 1 month was 13.81 in treated group vs 0.33 in untreated group (*P* = 0.003) Mean variation of MD at 1 month was −1.33 (±1.9) in treated group vs 1.77 (±2.5) in untreated group (*P* = 0.007)	N/A
Rootman (2013) [34]	III	17 treated 8 untreated	Prospective, non-randomised controlled	15 days	Intravitreal bevacizumab (1.25 mg)	No VA or VF or disc swelling improvement (*P* = 0.3, *P* = 0.4 and *P* = 0.1 respectively)	Non-insulin-dependent diabetes, hypertension, smoking
Prokosch (2014) [35]	III	30 treated patients and 30 untreated patients	Prospective, randomised controlled	3 days	Pentoxifylline (PFX) IV vs Pentoxifylline + fluocortolone (FC)	Change BCVA for PFX + FC patients was 0.11 ± 0.14 after 3 days and 0.21 ± 0.19 after 6 months, while there was no change in the BCVA score in PFX group at either of these time points (mean change BCVA after 3 days 0.0 ± 0.18, after 6 days 0.05 ± 0.19; *P* < 0.002 and *P* < 0.001, respectively). At 6 months after starting therapy MD in PFX patients was −14.4 ± 9.2 and −16.74 ± 3 in PFX + FC patients, comparison of the data showed no significant difference (*P* < 0.2)	N/A
Kinori (2014) [36]	III	24 treated 24 untreated	Retrospective case–control	14 days	Methylprednisolone (1 g/day)	Mean initial VA was 20/70 (LogMAR 0.54 ± 0.67) in the treated group and 20/69 (LogMAR 0.54 ± 0.49) in the control group (*P* = 0.8). At the end of follow-up, VA acuity for control group was 20/80 (0.60 in LogMAR) in the treated group and 20/53 (0.42 in LogMAR) in the control group (*P* = 0.3). VF showed defects in 2.4 ± 0.8 in the treated group and 2.0 ± 0.6 quadrants in the control group (*P* = 0.007). At final visit, quadrant involvement was 2.6 ± 0.9 in treated group and 2.2 ± 0.7 in control group (*P* = 0.07) No statistical difference was found between groups at the end of follow-up (*P* = 0.2).	Diabetes mellitus, dyslipidaemia, hypertension, ischaemic heart disease and smoking
Zhu (2015) [37]	IV	16	Case series	(6–18 days)	Enhanced extracorporeal counterpulsation (EECP)	10 eyes (62.5%) showed improvement of 3 or more Snellen lines. The median LogMAR VA in NAAION eyes was 0.92 [0.32; 1.92] before EECP and was 0.40 [0.22; 0.90] after the last EECP treatment. Significant difference in median change in VA in NAAION eyes between before EECP and after 12 h EECP (*P* = 0.003). Median MD before EECP was −15.90 dB (SD 5.81) vs −15.14 dB (SD 5.02) after 12-h EECP (*P* = 0.049)	Diabetes mellitus, dyslipidaemia, hypertension, history of ischaemic heart disease, smoking, previous cerebrovascular accident, alcoholism
Lyttle (2016) [38]	III	33 treated 26 untreated	Retrospective	15 days	Levodopa (100 mg levodopa / 25 mg carbidopa three times daily)	Among patients with ≤ 20/60 initial VA, treated participants had significant improvement (*P* < 0.0001) in the mean change from initial to final LogMAR VA of −0.74 ± 0.56 (95% CI, −0.98 to −0.50), while the mean change for the control group of−0.37 ± 1.09 (95% CI estimate, −1.00 to +0.26) was not significant (*P* = 0.23). A significant difference between groups was observed (*P* = 0.0086) with19/23 (83%) in the treated group improving and none got worse, compared with 6/14 (43%) in the control group improving while four (29%) worsened. The treated group had worse mean initial VF MD at −18.9 dB (±8.8) compared to the mean initial visual field MD of controls of −13.3 dB (±8.5) (*P* = 0.04). The groups were not found to be significantly different (*P* = 0.23), with the estimated difference in means at follow-up being 1.78 dB (95% CI, −1.19 to +4.74). The treated group had a mean reduction of 57.1% RNFLT to 73.2 (±33.2) μm, and control eyes had a mean reduction of 62.5% RNFLT to 85.4 (±19.0) μm compared to the initial RNFL thickness, but this was not statistically significant. No significant difference on VF and disc swelling (*P* = 0.23 and *P* = 0.75, respectively)	N/A
Sanjari (2016) [39]	IV	13	Case series	14 days	Intravitreal Fasudil (0.025 mg/0.05 mL)	At M3, BCVA improved from 1.69 ± 0.55 LogMAR at baseline to 0.93 ± 0.51 LogMAR (*P* = 0.004), RNFLT decreased from 173.5 ± 29.28 μm to 62.9 ± 5.97 μm (*P* = 0.003) and MD values changed from 24.60 ± 3.80 to 20.5 ± 6.50 (*P* = 0.005)	N/A
Aftab (2016) [40]	IV	24	Case series	4 weeks	Heparin IV / Warfarin PO	Significant VA improvement in 16 (66.7%), worsening in 1 (4%), average improvement was 5.6 LogMAR lines	Hypertension, dyslipidaemia, diabetes mellitus
Pakravan (2016) [21]	III	90 total 30 untreated	Randomised controlled	N/A	Steroid / normobaric oxygen with mask	Mean initial BCVA was 1.02 ± 0.63, 1.05 ± 0.7 and 0.76 ± 0.5 LogMAR in groups 1 (control), 2 (steroid) and 3 (oxygen), respectively (*P* = 0.293); corresponding values were 0.8 ± 0.45, 0.84 ± 0.45 and 0.58 ± 0.4 at month 1 (*P* = 0.127, 0.19 and 0.168, respectively). BCVA improved to 0.71 ± 0.46, 0.73 ± 0.36 and 0.59 ± 0.41 LogMAR at the 6-month follow-up point (*P* = 0.039, 0.048 and 0.195, respectively). Initial MD was 19.26 ± 7.02, 20.51 ± 4.68 and 19.3 ± 7.17 in groups 1, 2 and 3, respectively (*P* = 0.6). Corresponding values at month 1 were 20.26 ± 8.52, 19.52 ± 7.08 and 18.3 ± 7.45, (*P* = 0.6); and at month 6 were 18.42 ± 8.17, 17.66 ± 6.44 and 16.53 ± 6.32, respectively (*P* = 0.6). RNFLT at presentation was 166 ± 57, 184 ± 57 and 193 ± 65 μm in groups 1, 2 and 3, respectively (*P* = 0.2), which decreased to 73 ± 11, 87 ± 26 and 79 ± 19 μm at the final follow-up (all *P* < 0.001)	Exclusion of patients with diabetes mellitus or poorly controlled hypertension.
Weiss (2017) [41]	IV	10 total	Case series	(1–35 years)	Autologous bone marrow-derived stem cell therapy	VA improvement in bilateral vision in 80% of patients (*P* = 0.02) with an average of 3.53 Snellen lines. 73.6% of eyes treated gained vision (*P* = 0.01) and 15.9% remained stable in the post-operative period. The average LogMAR change in treated eyes was a gain of 0.364 (*P* = 0.008).	N/A
Pakravan (2017) [42]	III	83 treated 30 untreated	Case–control	14 days	IV erythropoietin and steroid /steroid alone	No significant difference between the 3 groups for BCVA (*P* = 0.8), MD (*P* = 0.8), RNFLT (*P* = 0.1) at 6 months	Hypertension, dyslipidaemia, ischaemic heart disease Exclusion of patients with diabetes mellitus or poorly controlled hypertension
Saxena (2018) [22]	II	19 treated 19 untreated	Double-blind randomised	1 month	Oral steroids (80 mg tapering dose)	Untreated group showed a median baseline BCVA of 0.8 LogMAR (range, 0–2.7 LogMAR), whereas treated group showed a median baseline BCVA of 1 LogMAR (range, 0.5–3 LogMAR; *P* = 0.16). The final median BCVAs of the untreated group and treated group were 0.6 LogMAR (range, 0–2.7 LogMAR) and 0.5 LogMAR (range, 0.2–1.8 LogMAR), respectively (*P* = 0.78). Both groups showed a statistically significant improvement in BCVA from baseline during 6-month follow-up (*P* = 0.01 and *P* = 0.003 for the untreated and treated groups, respectively); however, the treated group showed a greater change in vision compared with the untreated group. Superior and inferior RNFLT showed a greater reduction of oedema at the 1-month follow-up visit (*P* = 0.028 and *P* = 0.031, respectively) in the treated group compared with the placebo group. There was a greater change in the superior and inferior quadrants (*P* = 0.03 and *P* = 0.03, respectively) at the 1-month follow-up visit in the treated group compared with the untreated group. The percentage change in RNFLT in both groups was statistically similar.	Hypertension, dyslipidaemia, obstructive sleep apnoea Exclusion of patients with diabetes
Kalabova (2020) [43]	III	55	Retrospective	N/A	IV vasodilators alone or with IV corticosteroids	In the group treated only with IV vasodilator, mean VA at the beginning of NAAION was 0.356, and immediately after the end of therapy 0.439. Thus, VA improved by an average of 0.083. In the group with combined therapy, average VA before treatment was 0.398 and immediately after the end of therapy 0.429, i.e. VA improved by an average of 0.031. No significant difference was found between the groups in the change of VA (*P* = 0.7).	Hypertension, diabetes mellitus, dyslipidaemia, hypercoagulation states (hyperhomocysteinaemia), collagenosis, nocturnal hypotension, obstructive sleep apnoea syndrome, treatment for erectile dysfunction and smoking
Nikkhah (2020) [44]	II	Group A (systemic erythropoietin): 33 Group B (oral steroids): 32 Group C (control): 32	Randomised controlled	5 days	10,000 units of erythropoietin / 12 h for 3 days (group A)/ oral prednisone 75 mg /24 h tapered off in 6 weeks	55% of patients in group A (systemic erythropoietin) versus 34.3% in group B (oral steroids) and 31.2% in group C (control) had an improvement of at least 3 lines in the best-corrected VA at M6 (*P* = 0.04).	Exclusion of patients with systemic conditions such as diabetes or uncontrolled high blood pressure
Durbant (2021) [26]	III	41 treated 27 untreated	Retrospective unmasked and non-randomised	N/A	Intravitreal triamcinolone (4 mg/ 0.1 ml)	Higher proportion of patients improved VA by 2 lines or more in the treated group (49%) compared with the untreated group (11%, *P* = 0.01). Among patients injected before 15 days, the proportion improving by 2 lines or more (55% vs. 11%, respectively, *P* = 0.01) and by 3 lines or more (45% vs. 11%, respectively, *P* = 0.03) were significantly higher than in the untreated group. Visual field improvement was only observed in the subgroup of patients injected within 15 days with a significant improvement of the mean deviation (dB) within 6 months (*P* = 0.01).	N/A

*BCVA* best-corrected visual acuity, *EECP* enhanced extracorporeal counterpulsation, *FC* Fluocortolone, *IV* Intravenous, *MD* mean deviation, *N/A* not applicable, *PFX* Pentoxifylline, *PO* per os, *PSD* pattern standard deviation, *RNFL* retinal nerve fibre layer, *RNFLT* retinal nerve fibre layer thickness, *VA* visual acuity, *VAR* visual acuity rating, *VF* visual field

After unilateral involvement, bilateralisation at 5 years can occur in 9.5–24% of cases [45–47], causing severe visual disability. We recently showed that non-adherence to continuous positive airway pressure treatment by patients with severe obstructive sleep apnea syndrome (OSAS) increases the risk of contralateral NAAION by 5.5 [47].

Among novel strategies aimed at treating NAAION, treatment with a systemic endothelin receptor antagonist has recently emerged as a promising new strategy, for the following reasons:NAAION is associated in 75–80% of cases with OSAS [47–49]. The endothelin system is activated in OSAS patients, and endothelin 1 (ET-1) is associated with intermittent hypoxia, a major feature of OSAS [50, 51]. It is also involved in the physiopathology of cardiovascular disease (hypertension, myocardial infarction and/or vascular remodelling, all frequent comorbidities of OSAS).Endothelin 1 is implicated in vascular damage of the optic nerve. In animal models, the application of ET-1 directly to the optic nerve, or in the eyes, induces ischaemic optic neuropathy. An increase in the plasma levels of ET-1 was also found in NAAION patients [52].At the ocular level, bosentan, a duel ET-1 receptor antagonist, increases retinal and optic nerve blood flow in healthy humans and glaucoma patients [53].Bosentan is an already certified medication used in pulmonary arterial hypertension, and for digital ulcers associated with systemic sclerodermia, and has a good tolerance profile. While abnormally high levels of hepatic enzymes occur in approximately 10% of patients, with 3% of them discontinuing treatment, any hepatic toxicity can be easily detected [54].

### Objectives {7}

The *primary objective* of this trial is to compare the outcomes after 8 weeks of oral bosentan treatment vs. placebo, evaluated by changes in the automated visual field parameters at 3 months. The 3-month timeframe was chosen to assess both functional and anatomic evolution (resolution of optic disc swelling) [55].

The *secondary objectives* are to compare the peripapillary retinal nerve fibre thickness (RNFL) at 3, 6, 12 and 24 months after inclusion, visual function, i.e. visual acuity (VA) and visual field (VF), at 6, 12 and 24 months, quality of life at 3 and 12 months, inflammation markers and plasma levels of pre-proendothelin at 3 months, as well as the extent of bilateralisation of NAAION at 24 months, between the two groups (bosentan and placebo) of patients.

### Trial design {8}

This is a phase III, interventional, prospective, multicentre controlled randomised double-blind trial. The design of the trial is presented in Fig. 1.

**Fig. 1 Fig1:**
[figure not shown]
Trial design. PSG: polysomnography; AMBP: ambulatory blood pressure measurement; AE: adverse event; SAE: serious adverse event; VFQ-25: Visual Function Questionnaire 25; VA; visual acuity; VF: visual field; OCT: optical coherence tomography

## Methods: participants, interventions and outcomes

### Study setting {9}

This is a multicentre study including patients recruited in 6 French University (or University affiliated) Ophthalmology Centres, with recognised expertise in Neuro-Ophthalmology (Grenoble-Alpes, Bordeaux, Saint-Etienne, Angers and Paris). In Paris, two Academia-affiliated centres with high recruitment and expertise in neuro-ophthalmic disorders, including NAAION, are participating to the study (the Quinze-Vingts National Hospital Centre for Ophthalmology (CHNO) and the Adolphe de Rothschild Foundation Hospital).

### Eligibility criteria {10}

NAAION is diagnosed based on the standard criteria of recent (≤ 21 days), rapid and painless onset of VF loss, occurring with diffuse or sectorial swelling of the optic disc [56]. The trial’s inclusion and non-inclusion criteria are listed in Table 2. In each participating centre, possible differential diagnoses are carefully assessed by physicians with expertise in neuro-ophthalmology.

**Table 2 Tab2:** Inclusion and non-inclusion criteria

Inclusion criteria	Non-inclusion criteria
Age ≥ 50 years old	Pregnant or breast-feeding women^a^
Patients who signed the consent form	Patients with other acute or chronic intercurrent ocular pathology interfering with visual acuity or visual field (diabetes, drug-induced or other retinopathy, other optic neuropathy including uni- or contralateral glaucoma and/or intraocular pressure > 30 mmHg, advanced cataract, corneal opacities, amblyopia < 5/10, severe myopia > −6 diopters, retinal disease)
Patients affiliated with a national health insurance scheme or beneficiaries of such a scheme.	Simultaneous bilateral NAAION, occurring 1 month apart or less
	Evidence or suspicion of other causes of optic neuropathies considered as main differentials: 1/ giant cell arteritis causing arteritic anterior ischemic optic neuropathy (AAION) 2/ Optic neuritis (based on clinical examination, personal history of multiple sclerosis, contributive ancillary investigations) and 3/ compression/infiltration of the optic nerves, based on the clinical findings and orbital/brain imaging.
	Patients with systolic blood pressure below 100 mmHg
	Patient with orthostatic hypotension (20 mmHg drop in SBP and/or 10 mmHg drop in DBP when moving to a standing position)
	Neurological history of vascular or tumour-related changes to the visual field or other optic neuropathy
	Systemic inflammatory disease
	Known allergy to bosentan
	Patients with moderate to severe hepatic impairment (Child-Pugh class B or C), biliary cirrhosis (serum levels of liver aminotransferases, aspartate aminotransferases (ASAT) and/or alanine aminotransferases (ALAT), greater than three times the upper limit of normal, bilirubin greater than twice normal)
	Estimated glomerular filtration rate (GFR) < 30 ml/min/1.73 m^2^
	Patients treated with drugs whose efficacy may be reduced by activation of cytochrome P450, 2C9, 3A4 and 2C19 isoenzymes
	Patients treated with amiodarone
	Patients treated with one of the prohibited concomitant treatments in the study
	Patient treated with systemic corticosteroids (background treatment or treatment initiated at the time of NAAION diagnosis)
	Person deprived of liberty by judicial or administrative decision, adult protected by law, hospitalised person
	Ongoing participation in another clinical research study or in the exclusion period of another clinical study

^a^Due to potential pharmaceutical interactions, bosentan may render hormonal contraception ineffective. Therefore, women using hormonal contraception as the only method of contraception should be advised to use a complementary method of contraception or to use another reliable method of contraception. If there is any doubt about which method of contraception is most appropriate for the individual patient, the advice of a gynaecologist is recommended

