### Outcomes {12}

The *primary endpoint* (a) is the mean deviation in VF (in dB) 3 months after inclusion. This endpoint is considered sufficient to assess functional and anatomic recovery with the disappearance of optic disc swelling by this time [57].

The *secondary endpoints* are as follows: (b) peripapillary retinal nerve fibre thickness (RNFL) and macular ganglion cell layer thickness measured using SD-OCT at 3, 6, 12 and 24 months after inclusion; (c) visual function (VA using the ETDRS scale and VF) at 6, 12 and 24 months: (d) the extent of bilateralisation of NAAION at 24 months; and (e) quality-of-life parameters assessed using the visual function questionnaire (VFQ-25) [58] at 3 and 12 months.

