## Statistical methods

### Statistical methods for primary and secondary outcomes {20a}

Data from all patients included in this study will be included in the final analysis, following the modified intention to treat (mITT) principle. Data may be excluded from the analysis if an automated VF assessment was not obtained and/or VF parameter values are not reliable.

The number of patients presenting a major deviation to the protocol will be listed, and a sensitivity analysis on the per protocol population will be conducted. The major deviations will be reviewed by the trial’s data and safety monitoring board (DSMB).

The quantitative variables will be presented as means and standard deviations. The qualitative variables will be presented as numbers and percentages. Statistical analysis will be performed using STATA® Software Version 14.2 or higher (Stata Corporation [name]). Data normality will be evaluated graphically and tested using the Shapiro-Wilk test. The statistical tests will be interpreted considering a two-sided *p*-value < 0.05 as significant.

For the *primary endpoint analysis*, the progression in the MD (in decibels) of the VF between baseline (inclusion visit, D1) and the 3-month visit (M3) measured using automated perimetry, i.e. delta M3 – D1, will be compared between the two groups using a linear mixed effects model, with the group as a fixed factor. The study centre will be included in the model as a random effect, and the MD at baseline will be included as a covariate in the model.

A second model of the same type will be built, adjusted on the presence of OSAS and on other baseline parameters that potentially differ between the two groups (here the *Y* variable will be the difference in RNFL: M3 – D1). The quantitative variables will be log-transformed if their distribution is not normal, so as to satisfy the conditions required to apply linear models.

For the *secondary endpoint analyses*, the same type of analysis as that used for the primary endpoint will be used for VA. Other comparisons between the two groups will be made using the Student *t* test or the Mann–Whitney *U* test (depending on the normality of the data distribution) for quantitative variables. Qualitative variables will be analysed using the chi-squared test (or the Fisher exact test depending on the theoretical number of patients).

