### Methods in analysis to handle protocol non-adherence and any statistical methods to handle missing data {20c}

All available data will be included in the final mITT analysis, even in case of protocol non-adherence. However, missing data will not be replaced.

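### Bilateralisation at 24 months has no at-risk set and no use of follow-up time, although Table 2 does not clearly exclude patients whose fellow eye has already had NAAION

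*Protocol article*

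**What the plan says.** Under Outcomes {12}, secondary endpoint (d) is "the extent of bilateralisation of NAAION at 24 months"; the abstract calls it the "rate of NAAION bilateralisation at 2 years". The abstract and the closing paragraph of the Discussion list the effect on bilateralisation among the three questions the trial is meant to address.

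On who can enter, Table 2 under Eligibility criteria {10} lists as a non-inclusion criterion "Simultaneous bilateral NAAION, occurring 1 month apart or less". Another entry reads "Neurological history of vascular or tumour-related changes to the visual field or other optic neuropathy". The section on assessment and collection of outcomes {18a} describes perimetry and OCT as starting with the healthy eye.

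On analysis, section {20a} says "Data from all patients included in this study will be included in the final analysis" under a modified intention-to-treat principle, with possible exclusion where the visual field is missing or unreliable. Visual acuity is modelled like the primary endpoint. For the rest: "Qualitative variables will be analysed using the chi-squared test (or the Fisher exact test depending on the theoretical number of patients"). Section {20c} adds that "missing data will not be replaced". Bilateralisation is not named in the statistical section. No at-risk set, denominator or time-to-event method is given for it.

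**The concern.** Bilateralisation can occur only in a patient whose fellow eye has not yet had NAAION. The protocol's own background figure is conditioned this way: after unilateral involvement, "bilateralisation at 5 years can occur in 9.5–24% of cases". A 1-month limit on bilateral cases serves a purpose only if cases further apart may enter. Such patients would count in the denominator and could never contribute an event.

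Separately, a fixed-time comparison of patients with a month-24 status makes no use of the months observed in those who left earlier. Loss could differ by arm. The allowance in Sample size {14} includes interruptions for side effects of bosentan, and section {11b} lets study participation, not only treatment, end on raised liver enzymes.

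At stake are the absolute 24-month risks and their difference, for an endpoint that the trial puts forward prominently but expects to observe rarely.

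**Working it through.** **Figures in the protocol.** It gives no expected rate, effect or power for bilateralisation, so there is no figure of that kind to reproduce. The enrolment total does reproduce: 2 × 36 = 72; 20% of 72 = 14.4, taken as 14; 72 + 14 = 86, or 43 per arm.

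**Step 1: can a patient not at risk enter?**
- Table 2 excludes second-eye NAAION only if it occurred within 1 month.
- The entries on other optic neuropathy most naturally mean other than NAAION, but could be read to include an earlier episode in the fellow eye.
- Section {18a} presumes a healthy fellow eye.

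The first point leaves sequential cases eligible, the third presumes there are none, and the second does not settle it. The share q of such patients is not in the documents; I take 0–20% as an assumption.

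**Step 2: expected events.** Inputs are the 5-year risk r5 = 9.5–24% (Background {6a}) and N = 86 (Sample size {14}). Assuming a constant hazard, 2-year risk = 1 − (1 − r5)^(2/5).
- r5 = 0.095: 1 − 0.905^0.4 = 0.039, so 86 × 0.039 = 3.4 events (1.7 per arm).
- r5 = 0.24: 1 − 0.76^0.4 = 0.104, so 86 × 0.104 = 8.9 events (4.5 per arm).

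These counts take all 86 as at risk and no treatment effect. At q = 20% they fall to 2.7 and 7.2.

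**Step 3: effect of patients not at risk.** Reported risk = (1 − q) × true risk in each arm. For illustration, suppose treatment halves the risk:

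| Placebo risk | q | Reported placebo | Reported bosentan | Difference (points) | Ratio |
|---|---|---|---|---|---|
| 3.9% | 0 | 3.9% | 2.0% | 2.0 | 0.5 |
| 3.9% | 10% | 3.5% | 1.8% | 1.8 | 0.5 |
| 3.9% | 20% | 3.1% | 1.6% | 1.6 | 0.5 |
| 10.4% | 0 | 10.4% | 5.2% | 5.2 | 0.5 |
| 10.4% | 10% | 9.4% | 4.7% | 4.7 | 0.5 |
| 10.4% | 20% | 8.3% | 4.2% | 4.2 | 0.5 |

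At q = 10% there are 43 × 0.9 = 38.7 patients at risk per arm, and at q = 20% there are 34.4. Restricting to them loses no events, because the others cannot have one.

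**Step 4: follow-up time discarded.** As an illustration only, suppose 14 of 86 leave event-free after 1 year on average. Observed time is then 72 × 2 + 14 × 1 = 158 patient-years (ignoring the little time lost after events). The available-case comparison drops 14 of these, about 9%. The figure of 14 is borrowed from Sample size {14}, where it also covers premature stopping; it is not a 24-month loss rate.

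**Step 5: what a test could show.** With 43 per arm, power to detect a halving is 8% (3.9% risk) to 14% (10.4% risk) by the normal approximation, and 0.3% to 5.6% with Fisher's exact test.

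**The case against.** Several objections have force.

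- **The denominator is not stated to be all 86.** A reader might infer a wrong denominator. The text does not show that: bilateralisation is not named in the statistical section, non-replacement implies available cases, and patients without a reliable visual field may be excluded. The denominator is not restricted to patients at risk, which is a weaker statement. A fuller protocol or analysis plan may define the set. What stands is that the general rule is stated, and that Table 2 and the examination procedures disagree in this document.
- **Patients not at risk do not bias the comparison.** Earlier fellow-eye NAAION is a baseline feature, so randomisation balances it in expectation. This is right. The damage is dilution of the absolute risks and their difference, and zero such patients is compatible with the wording on the healthy eye.
- **Drop-outs are handled.** A reader might infer that they are ignored or counted as event-free. The protocol handles them by omission, and nothing supports counting them as event-free.
- **Unequal loss is conjecture.** Treatment lasts 8 weeks, and stopping it need not end follow-up. This also stands: the documents make unequal loss possible but do not show it.
- **Fisher's test suits sparse data.** It does, and it remains valid under the null hypothesis. It does not supply a 24-month risk that uses the observed time.
- **A better method would rarely change the conclusion.** With so few events that is true, and it limits the claim to estimation.

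**Conclusion.** The point holds as a weakness of definition and method, not as a demonstrated error. Earlier NAAION in the fellow eye is not clearly excluded, the procedures assume it is absent, and the only applicable analysis rule neither restricts to patients at risk nor uses follow-up time.

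The size of the dilution is the factor 1 − q: none if every fellow eye is unaffected, and at most one fifth over the assumed range. In the halving example that is at most about 1 percentage point on a difference of 5.2. The risk ratio and the null test are not biased in expectation by this. The cost of discarding follow-up cannot be computed from the documents, since neither the 24-month loss nor its split by arm is given.

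The assumptions are a constant hazard for the 2-year risk, q of 0–20%, and the illustrative halving. Scarcity of events, about 3–9 in total, dominates all of this.

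**What to change.** 1. Reconcile Table 2 with section {18a}: state whether a patient with NAAION in the fellow eye more than 1 month earlier can be included.
2. Define the bilateralisation analysis set as randomised patients with no NAAION in the fellow eye before inclusion, and report how many are left out in each arm.
3. Replace the fixed-time chi-squared or Fisher test for this endpoint with time from inclusion to fellow-eye NAAION, censored at the last visit. Report the Kaplan-Meier 24-month risk per arm and the risk difference with 95% CI. If a test is wanted, use an exact or permutation log-rank test.
4. Present the result as estimation.

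The cost is a few sentences and a slightly smaller denominator. Fellow-eye history and onset date, or failing that the visit of detection, must be taken from the ophthalmological records; the article does not say that they are recorded as such. The Kaplan-Meier risk assumes that, within an arm, patients who leave have the same later risk as those who stay, so numbers and reasons for leaving should be shown by arm. The comparison remains underpowered whichever method is used.
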